## Assignment of interventions

### Allocation sequence generation {16a}

A minimisation algorithm will be used to avoid imbalance of age and disease severity across arms at baseline. The algorithm will randomly allocate patients to each arm with each newly recruited patient having an 80% probability of being allocated to the arm which achieves the best balance of age and disease severity, and a 20% probability of being allocated to the other arm. The two criteria used to minimise will be age, dichotomised at the median age of participants of the PRIME cross-sectional study, and Hoehn and Yahr stage, categorised as stages 1–2, stages 3–4, and stage 5. In this way, atypical and cognitively impaired participants should be well balanced but we will of course examine this at baseline and if necessary adjust for these predictors in our models. In the long run, this minimisation process will be expected to achieve a 1:1 allocation ratio.

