### Eligibility criteria {10}

The eligibility criteria for trial participation are shown in Table 1. Where there is uncertainty about the diagnosis, a decision will be reached from discussion and consensus between the patient’s usual treating clinician and the PRIME trial team. Patients must be able to provide informed consent to participate or where unable to do, there must be availability of a close friend or relative to act as a personal consultee. We have designed this complex intervention trial to ensure inclusion of under-represented groups with particular regard for those with cognitive impairment or dementia in order to maximise the generalisability of the findings. Cognitive impairment is common in people with parkinsonism [11], and this group is often precluded from participating in clinical research [12, 13]. Recognising the physical and psychological negative impact that caregivers may experience [14, 15], up to three informal caregivers, per person with parkinsonism, will also participate (Table 1).

**Table 1 Tab1:** Inclusion and exclusion criteria for patients and caregivers

Group	Criterion	Definition
**Patients, inclusion**	Age	≥ 18 years
	Diagnosis of parkinsonism	Includes idiopathic Parkinson’s disease, progressive supranuclear palsy, corticobasal degeneration, multisystem atrophy, dementia with Lewy Bodies, vascular parkinsonism or primary progressive freezing of gait
	Location	Be resident within the geographical catchment area of the trial site
	Willingness	Be willing to participate
**Patients, exclusion**	Cause of parkinsonism	Drug, infection or toxin induced parkinsonism
	Capacity	Lack capacity to participate and do not have anyone who can be a consultee to provide advice regarding the patient’s wishes and views
	Decision of clinician	Current medical, cognitive or psychosocial issue or co-enrolment in other study that, in the opinion of the site investigator, would interfere with adherence to study requirements
**Caregivers, inclusion**	Age	≥ 18 years
	Provision of care	Provide informal care or support for a patient with parkinsonism
	Willingness	Be willing to participate
	Capacity	Have the ability to provide informed consent to participate
**Caregivers, exclusion**	Formal care	Professional caregivers who are paid to deliver care
	Person with parkinsonism not participating	Unwillingness or ineligibility of person for whom they provide care

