*=outcomes that will be completed by a representative who knows the patient well, where the patient cannot self-complete; #=outcome measures which will also be assessed at 3, 6, 9, 15, 18 and 21 months. The following parameters will be assessed at baseline and/or at 12/24 months but are not outcome measures per se: fracture risk using FRAX* [45] and/or QFracture* [46] with bone densitometry where required; habitual dietary intake using the European Prospective Investigation into Cancer Food frequency questionnaire* [47]; comorbidity using Cumulative Illness Rating Scale-Geriatrics [48]; cognition using Montreal Cognitive Assessment (MoCA) [49]. Place and date of death, where applicable, will also be captured

**Table 3 Tab3:** Outcome measures for caregivers which will be measured at baseline, 12 and 24 months

Domain	Outcome	Measurement tool/method, where one is available
**Caregiver measures**	Care-related quality of life	Carer Experience Scale (primary outcome) [20]
	Caregiver quality of life (PD-specific)	Parkinson’s Disease Questionnaire for carers (PDQ-carer) [50]
	Caregiver burden	Zarit Burden Interview [51]
	Caregiver activation level	Patient Activation Measure 13 UK (CG-PAM) [41]
	Caregiver coping strategy	BriefCOPE [38]
	Care (including relationship to recipient, living with recipient, intensity of caring, duration of care duties, tasks of caring)	N/A
**Health**	Frailty	Survey of Health, Ageing, and Retirement in Europe (SHARE-FI) 75+ [25]
	Sarcopenia	SARC-F and *SARC*-*CalF* [28]
	Malnutrition risk	Malnutrition Universal Screening Tool (MUST)
	Nutritional risk	Seniors in the community: risk Evaluation for Eating and Nutrition (SCREEN II)-14 item version [29, 30]
**Performance**	Physical performance	Short physical performance battery (SPPB) Time up and go test (TUG)
	Physical activity	Incidental and Planned Exercise Questionnaire for the Usual week (IPEQ-WA) [32]
	Grip strength	Hand-held dynamometer
**Social**	Loneliness/social isolation	3-item Revised-UCLA Loneliness Scale plus a single item direct measure of loneliness [35]
**Economic measures**	Caregiver costs	The Caregiver Indirect and Informal Case Cost Assessment Questionnaire [52]
**Process measures**	Frequency and type of engagement with PRIME Parkinson care (intervention arm)	N/A

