## Statistical methods

### Statistical methods for primary and secondary outcomes {20a}

To determine if PRIME Parkinson care can improve goal attainment and impact the secondary outcomes, the primary analysis to determine whether PRIME Parkinson care can achieve goal attainment and improve health-related quality of life, symptom burden and hospitalisations will be conducted according to the intention to treat principle. Participants who provide primary outcome data will be included in the analysis in their allocated group (see below concerning missing outcome data). The intervention effect will be estimated as the coefficient of a binary covariate indicating treatment allocation in a linear regression with the goal attainment score as the outcome variable and with age and Hoehn and Yahr stage (minimisation variables) as additional covariates. We will examine the outcome at 24 months first, and if we observe no benefit, we will test if this was observed at 12 months. The estimated effect will be presented together with 95% confidence intervals and *p*-value. This approach to the analysis will be adapted to the participant secondary outcome measures, and to the outcome measures completed by caregivers. To determine the effect of PRIME Parkinson care versus usual care on those caring for, living with, or supporting a person with parkinsonism, robust standard errors will be employed to accommodate correlation between caregivers of the same participant.

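### The balance-triggered adjustment for atypical diagnosis and cognition in {16a} does not agree with the fixed primary model in {20a}; the two should be reconciled by prespecification

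*Protocol article*

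**What the plan says.** Under Allocation sequence generation {16a}, the protocol article names the balancing factors: "The two criteria used to minimise will be age, dichotomised at the median age of participants of the PRIME cross-sectional study, and Hoehn and Yahr" (the latter split into three groups). It then draws an inference about two factors that are not in the algorithm: "In this way, atypical and cognitively impaired participants should be well balanced". The same sentence continues: "we will of course examine this at baseline and if necessary adjust for these predictors in our models".

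Under Statistical methods for primary and secondary outcomes {20a}, the intervention effect comes from a linear regression of the goal attainment score on allocation, "with age and Hoehn and Yahr stage (minimisation variables) as additional covariates". Neither diagnosis nor cognition is listed there, and nothing makes the covariate list depend on observed balance. The same approach is to be adapted to the secondary and caregiver outcomes.

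The two factors matter to this population. Table 1 admits a wide range of diagnoses besides idiopathic disease, and Eligibility criteria {10} states: "Cognitive impairment is common in people with parkinsonism". The notes to Table 2 list the MoCA among parameters taken at baseline and/or at 12/24 months, so this text does not guarantee a baseline value.

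**The concern.** The two sections give different accounts of the model. {20a} has a closed covariate list. {16a} opens that list to two further factors on a condition that is not defined: there is no threshold, no coding for either factor, no indication of which models are meant, and no statement of whether the adjusted result would replace or accompany the {20a} result.

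The condition is also the wrong one. A baseline covariate earns its place in a randomised comparison by predicting the outcome, not by happening to differ between arms. If the two factors are predictors, as {16a} calls them, adjusting only when they look imbalanced gives up precision in the many trials where they look balanced. The reported interval and p-value then do not match the procedure that produced them. At stake are some precision, the calibration of the main test, and a choice left to the analyst that need not exist.

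**Working it through.** **1. The plan's own figure.** Inputs from Sample size {14}: standardised effect 0.5, 90% power, 20% attrition. A two-sided 5% level is assumed for patients, because the 5% level is stated only in the caregiver calculation.

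- n per arm = 2 × (1.960 + 1.282)² / 0.5² = 84.1, so 85 (the t-based solution is 85.03).
- 85 / 0.8 = 106.25, so 107 per arm and 214 in total. The stated figures reproduce.

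**2. How far the balance inference can be relied on.** Minimisation balances its own factors, and others only through their link with those. As a limiting case, take a factor with 20% prevalence (assumed) and no link to age or stage:

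- SD of the between-arm difference = √(0.2 × 0.8 × 4 / 214) = 0.0547, or 5.5 percentage points.
- Chance of a difference above 5 points: 36%. Above 10 points: 7%.

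Any link with age or stage reduces these figures.

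**3. What a balance-triggered rule does.** The rule was simulated with 170 analysed patients (85 per arm) and 6,000 runs per scenario. None of the following is in the document:

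- simple 1:1 allocation;
- 15% atypical and 30% cognitively impaired;
- a condition read as a balance test at p<0.05 or p<0.20, applied to each factor;
- the two factors together explaining a share R² of outcome variance.

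Age and stage are not simulated. R² is therefore to be read as a share of the variance left after them, and the effect of 0.5 as scaled to that remaining SD.

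Two independent tests at 5% flag at least one factor with probability 1 − 0.95² = 9.75%. The simulation gave 9–10%, so a p<0.05 rule leaves both factors out about 90% of the time.

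Type I error (%), nominal 5%:

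| R² | Trigger p<0.05 | Trigger p<0.20 | Always adjust | Best of four covariate sets, chosen on outcome |
|---|---|---|---|---|
| 5% | 4.3 | 4.2 | 4.6 | 6.1 |
| 10% | 4.7 | 4.4 | 4.9 | 7.3 |
| 20% | 4.5 | 3.8 | 4.7 | 8.0 |
| 30% | 4.0 | 3.4 | 5.2 | 9.3 |

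Power (%) at a true effect of 0.5:

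| R² | Trigger p<0.05 | Always adjust | Loss |
|---|---|---|---|
| 5% | 89.4 | 90.5 | 1.1 |
| 10% | 90.2 | 92.4 | 2.2 |
| 20% | 91.5 | 95.4 | 3.9 |
| 30% | 91.7 | 97.4 | 5.7 |

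The Monte Carlo standard error is about √(0.05 × 0.95 / 6000) = 0.3 points for type I error and √(0.9 × 0.1 / 6000) = 0.4 points for power. The conservatism at small R² is therefore close to noise, and the pattern is clear only at the larger values.

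**4. Analytic check of the always-adjust column.** Power = Φ(0.5/√(1 − R²) × √(85/2) − 1.960). With R² = 0 this is Φ(3.260 − 1.960) = 90.3%. With R² = 5%, 10%, 20% and 30% it gives 91.7%, 93.0%, 95.4% and 97.4%, in line with the simulation.

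**The case against.** The strongest reply is that {20a} already fixes the primary model. The sentence in {16a} sits in the randomisation section, speaks only of models in general, and can be read as promising a supplementary analysis. This stands in part. A reader might infer that the primary model itself is data-driven, and the article does not establish that. It does not exclude it either, so what remains is a conflict between two sections that has to be settled.

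A reader might also infer that the headline p-value is inflated. That is not supported. A mechanical balance test errs on the conservative side. The 6.1–9.3% figures need an analyst who picks the most favourable covariate set after seeing outcomes, whereas {16a} speaks of examining baseline data.

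Third, the article promises a date-stamped analysis plan before data analysis ({31c}), which could fix the covariates. That is fair, and missing detail is not the complaint. The article states a rule, and an analysis plan with a fixed list would have to override it.

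Fourth, the figures rest on assumptions. This stands. The imbalance calculation ignores the carry-over from age and stage that the article relies on. The power gain counts only variance explained beyond age and stage. No figure in the article shows how strongly diagnosis or cognition predicts attainment of individually set goals.

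**Conclusion.** The point holds as an inconsistency with an easy remedy. {16a} makes adjustment for atypical diagnosis and cognitive impairment depend on observed baseline balance, while {20a} gives a fixed list without them.

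If the {16a} rule were applied mechanically at p<0.05, the cost would be about 1 to 6 points of power against prespecified adjustment, with a type I error of about 4.0–4.7% (down to 3.4% with a p<0.20 trigger). The power loss assumes that the two factors explain 5–30% of outcome variance beyond age and stage, and it shrinks towards nothing if they explain less. The assumed prevalences of 15% and 30% also enter.

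The undefined condition leaves discretion that could do harm only if exercised with outcomes known; nothing in the article says it would be. The trial's validity and its sample size are not in question.

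**What to change.** Choose one of two courses and make {16a} and {20a} agree.

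- **Preferred.** In {16a}, remove the words that make adjustment depend on inspecting balance. In {20a}, add diagnosis group (idiopathic Parkinson's disease versus other parkinsonism, known at eligibility) and baseline cognition as covariates in the primary model, whatever the observed balance.
- **Alternative.** Keep the {20a} model as the sole primary model and name the model further adjusted for diagnosis and cognition as a prespecified sensitivity analysis.

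In either case, confirm that the MoCA is taken at baseline, since the Table 2 notes leave this open, and state how it is coded. For patients without a usable score, use a missing-value indicator or a separate untestable/impaired category. Simple mean imputation should be avoided, because it would assign average cognition to patients who may be the most impaired, in a trial that deliberately includes them.

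The cost is a sentence or two of text and two or three extra model terms. The sample size stays at 85 analysed per arm and 214 recruited.

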### Concealment mechanism {16b}

Patients will be randomised after eligibility and consent have been confirmed at Visit 1, using an online randomisation system (Sealed Envelope, London, UK).

### Implementation {16c}

A member of the trial team will log onto the online randomisation system, enter the minimisation variables and request randomisation. The online system will generate the allocation code which will be displayed on screen. The allocated arm will be recorded on the password-protected IT platform and the participant informed by letter of the result. Members of the trial team who are conducting the blinded assessments will not have access to the allocated arm on the password-protected IT platform.

## Assignment of interventions: blinding

### Who will be blinded {17a}

Only the assessors who make 3-monthly phone calls to the patients will be blinded. Patients will be encouraged not to disclose their allocation to the assessor during these phone calls.

### Procedure for unblinding if needed {17b}

Not applicable.

## Data collection and management

### Plans for assessment and collection of outcomes {18a}

Data will be collected via participant-completed questionnaires on paper or electronically at Visit 1 (0 months), the mid-point assessment (12 months) and Visit 2 (24 months) and during the 3-monthly phone calls. Where a participating patient lacks capacity and is unable to complete the questionnaires, a representative will complete them on their behalf. The above methodology from screening through to follow-up is summarised in a flow diagram (see Fig. 1).

**Fig. 1 Fig1:**
[figure not shown]
A flow diagram summarising participant flow through the study from screening through to follow-up

### Plans to promote participant retention and complete follow-up {18b}

Data on protocol violations, eligibility and recruitment rate will be reported. If randomised to the intervention arm, participants may opt out of interventions offered, but remain enrolled in the trial and therefore continue to complete questionnaires, undergo assessments and allow researchers access to their medical records. Patients, representatives where relevant and caregivers will receive phone or text message reminders to complete the questionnaires, depending on their preference.

### Data management {19}

When a participant consents to take part, they will be allocated a unique participant identification number. Consent forms and clinical letters with personal identifiable data, and completed paper questionnaires will be stored in a locked filing cabinet. Personal and research data entered directly onto the password-protected IT platform by participants or a member of the trial team and maintained within the University of Bristol will only be accessible to members of the trial team. Information capable of identifying participants will not be removed from the University of Bristol or the site nor will it be made available in any form to those outside the trial team, with the exception of National Health Service Digital for linkage to routine data. Participant details will be anonymised in all publications that result from the trial.

### Confidentiality {27}

The principles of confidentiality will be adhered to. Data will be collected and retained in accordance with the Caldicott Principles, UK Data Protection Act 2018 and General Data Protection Regulation. Personal data will not be kept for longer than is required. All data analysis will take place on encrypted, password-protected computers. No data will be released from the password-protected IT platform to any unauthorised third party without the written approval of Chief Investigator. Data will be available only for monitoring by the Research Ethics Committee or regulatory agencies. An archiving plan will be developed for all trial materials in accordance with the Sponsor’s archiving policy and trial materials will be archived for 5 years from the end of the trial.

### Plans for collection, laboratory evaluation and storage of biological specimens for genetic or molecular analysis in this trial/future use {33}

Not applicable. No biological samples will be collected as part of this trial.

## Statistical methods

### Statistical methods for primary and secondary outcomes {20a}

To determine if PRIME Parkinson care can improve goal attainment and impact the secondary outcomes, the primary analysis to determine whether PRIME Parkinson care can achieve goal attainment and improve health-related quality of life, symptom burden and hospitalisations will be conducted according to the intention to treat principle. Participants who provide primary outcome data will be included in the analysis in their allocated group (see below concerning missing outcome data). The intervention effect will be estimated as the coefficient of a binary covariate indicating treatment allocation in a linear regression with the goal attainment score as the outcome variable and with age and Hoehn and Yahr stage (minimisation variables) as additional covariates. We will examine the outcome at 24 months first, and if we observe no benefit, we will test if this was observed at 12 months. The estimated effect will be presented together with 95% confidence intervals and *p*-value. This approach to the analysis will be adapted to the participant secondary outcome measures, and to the outcome measures completed by caregivers. To determine the effect of PRIME Parkinson care versus usual care on those caring for, living with, or supporting a person with parkinsonism, robust standard errors will be employed to accommodate correlation between caregivers of the same participant.

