### Outcomes {12}

The primary outcome for patients is goal attainment which will be measured prospectively at 3 monthly intervals using the Bangor Goal-Setting Interview [19]. The primary outcome measure for patients will be analysed whereby an overall, unweighted mean rating for attainment across goals will be calculated at each evaluation point by dividing the sum of the ratings for all goals set by the participant by the number of goals set. Goal attainment will be additionally analysed with goals weighted according to the importance ratings stated by the participant at the goal-setting interview conducted at Visit 1. The primary outcome for caregivers is care-related quality of life measure using the Carer Experience Scale [20]. Outcome measures for patients and caregivers are described in Tables 2 and 3, respectively. A separate qualitative study will be carried out to explore the experiences of patients and caregivers recruited to the trial, and of hospital staff involved in the care of people with PD alongside staff involved in the delivery of the intervention. This will be reported separately.

**Table 2 Tab2:** Outcome measures for patients which will be measured at baseline, 12 and 24 months

Domain	Outcome	Measurement tool/method where one is available
**Primary outcome measure**	Goal attainment	Bangor Goal-Setting interview [19]
**Parkinson’s specific measures**	Parkinson’s disease assessment	MDS-Unified Parkinson’s Disease Rating Scale (MDS-UPDRS) [21]
	Non-motor symptom burden	MDS Non-Motor Rating Scale (MDS-NMS)* [22]
	Parkinson’s-related quality of life	Parkinson’s Disease Questionnaire (PDQ-39)* [23]
**Health**	Fear of falling	Iconographical Fall Efficacy Scale (ICON-FES)-short version [24]
	Global impression of change	Patients’ Global Impression of Change (PGIC) Clinician Global Impression of Change (CGI-I)
	Frailty	SHARE-FI 75+ (Phenotypic frailty tool) [25] Pictorial fit frail scale* [26] Clinical frailty scale [27]
	Sarcopenia	SARC-F* and *SARC*-*CalF** [28]
	Malnutrition risk	Malnutrition Universal Screening Tool (MUST)
	Nutritional risk	Seniors in the community: risk Evaluation for Eating and Nutrition (SCREEN II)-14 item version* [29, 30]
	Delirium	4AT tool for delirium assessment [31]
**Physical performance**	Physical performance	Short physical performance battery (SPPB) Time up and go test (TUG)
	Physical activity	Incidental and Planned Exercise Questionnaire for the Usual week (IPEQ-WA)* [32]

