### Sample size {14}

In the GREAT trial, the mean score for goal attainment at baseline was approximately 3.5 (SD 1.6) [55]. To detect a standardised effect size of 0.5 between groups (regarded as a moderate effect size [57] with 90% power, we would need 85 in each group. To allow for 20% attrition, this sample size has been inflated to give a total sample size of 214, with 107 patients in each arm. In terms of caregivers, a previous study has estimated that up to 80% of people with moderate to advanced Parkinson’s have an informal caregiver [58]. If 80% of the 214 recruited patient participants have an informal caregiver and 70% of these agree to take part, this would result in 120 caregiver participants (60 in each arm). With this number of caregiver participants, we could detect a difference of half a standard deviation in the primary outcome measure with 80% power and at a 5% significance level. This is equivalent to a 9 point difference in the CES index score, based on Rand et al. who reported a mean CES index score of 68.70 with a standard deviation of 17.78 amongst carers of adults using social care support in England [59]. We will have slightly greater power because we will recruit up to 3 caregivers per patient, although these will not be independent observations

Patients will be recruited predominantly through three routes. The first is where they will have expressed written interest in hearing about further research on a consent form through participating in other research studies. Secondly, they may be identified by the trial team from current hospital admissions or clinic lists. Thirdly, they may hear about the trial through local advertising or on social media. Potential participants will be sent an invitation pack containing a letter of invitation, a Patient Information Brochure, a pre-paid reply slip and a consent form, which is for information only. It will also include the equivalent documents for a potential caregiver who may wish to take part. If the team has not heard from the potential participant within 2 weeks of posting the invitation pack to them, they will receive a phone call and all questions will be answered. Potential participants and caregivers who indicate that they are interested in taking part, either by phone or by posting back the reply slip(s), will receive an appointment letter for Visit 1 with the relevant questionnaire booklet or a link to electronic questionnaires, depending on their preference.

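### The primary model leaves out the baseline goal-attainment score that Table 2 schedules; the analysis is valid and reaches its stated power, but gives up precision

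*Protocol article*

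**What the plan says.** All references are to the protocol article.

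- **Model, {20a}.** The effect comes from a linear regression and is the coefficient of the allocation indicator. The model is set up "with the goal attainment score as the outcome variable and with age and Hoehn and Yahr stage (minimisation variables) as additional covariates".
- **Timing, {20a}.** "We will examine the outcome at 24 months first, and if we observe no benefit, we will test if this was observed at 12 months".
- **Outcome, {12}.** The analysed quantity is the score itself and not a change from baseline: "an overall, unweighted mean rating for attainment across goals will be calculated at each evaluation point".
- **Baseline measurement, {12}.** Goal attainment is the first row of Table 2, whose title reads "Outcome measures for patients which will be measured at baseline, 12 and 24 months".
- **Balance, {16a}.** Minimisation uses age and Hoehn and Yahr stage. Further adjustment is allowed if needed, but the sentence concerns atypical and cognitively impaired participants. Baseline attainment is not mentioned.
- **Sample size, {14}.** "To detect a standardised effect size of 0.5 between groups" and "with 90% power, we would need 85 in each group". The total is inflated to 214 for 20% attrition.
- **Other outcomes, {20a}.** The approach is to be adapted to the secondary and caregiver outcomes. Their covariates are not listed.

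**The concern.** When an outcome is scored on the same scale at baseline and follow-up, the baseline value is the usual first candidate for a covariate. Here it is scheduled but has no route into the primary estimate: not through the covariate list, a change score, the minimisation or the conditional adjustment in {16a}. Because {20a} names the covariates, this is a stated choice and not a detail left open for the statistical analysis plan.

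Two things are at stake. The first is precision: variation in follow-up scores that baseline could explain stays in the residual. The second is the single realised trial: if one arm happens to start with higher attainment, part of that difference remains in the estimate. Patients set their own goals and may start from quite different levels, and age and Hoehn and Yahr stage need not capture that.

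**Working it through.** **Inputs**

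- From {14}: standardised effect 0.5, power 90%, 85 per arm, 20% attrition, total 214.
- SD 1.6, also from {14}: "the mean score for goal attainment at baseline was approximately 3.5 (SD 1.6" points. This comes from an earlier external trial. I use it for both baseline and follow-up, so the target effect is 0.5 × 1.6 = 0.8 points.
- Two-sided 5% significance. For patients this is an assumption; {14} states a level only for caregivers ("with 80% power and at a 5% significance level"). Two-sided 5% reproduces the 85; one-sided 5% would give 69.
- r, the correlation of baseline with 24-month attainment. The document does not give it, so I show 0.2, 0.3 and 0.5.
- Any contribution of age and Hoehn and Yahr stage is ignored.

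**Step 1. The plan's own figure.** A two-sample comparison at 0.5 SD, two-sided 5% and 90% power needs 85 per arm (t-test solution 85.03). Then 85 / 0.8 = 106.25, rounded up to 107 per arm, or 214 in total. Both figures reproduce, so the planned size does not rely on baseline adjustment.

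**Step 2. Precision with adjustment.** Adding the baseline score multiplies the residual variance by 1 − r². The effect in residual SD units becomes 0.5 / √(1 − r²), and the standard error becomes 1.6 × √(1 − r²) × √(2/85). Power is from the two-sample t-test with 85 per arm.

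| Assumed r | 1 − r² | SE of effect (points) | Power |
|---|---|---|---|
| 0 (as planned) | 1.00 | 0.245 | 90.0% |
| 0.2 | 0.96 | 0.240 | 91.1% |
| 0.3 | 0.91 | 0.234 | 92.5% |
| 0.5 | 0.75 | 0.213 | 96.3% |

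Put the other way, at r = 0.5 an unadjusted analysis would need 85 / 0.75 ≈ 113 analysed per arm to match 85 with adjustment.

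**Step 3. Chance imbalance.** The baseline difference between arms has standard error 1.6 × √(2/85) = 0.245 points, so its 95% limit is 1.96 × 0.245 = 0.48 points. With equal SDs at baseline and follow-up, the follow-up score regresses on baseline with slope r, so a difference D moves the unadjusted estimate by r × D:

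- r = 0.2: 0.2 × 0.48 = 0.10 points
- r = 0.3: 0.3 × 0.48 = 0.14 points
- r = 0.5: 0.5 × 0.48 = 0.24 points

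Against the 0.8-point target these are about 12%, 18% and 30%, at the edge of what chance would produce.

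**Step 4. Does a baseline score exist in both arms?** Table 2 applies to all patients and includes goal attainment. The Visit 1 goal-setting interview is described under the intervention ({11a}, care management), but controls cannot be rated on attainment unless they too have set goals. Consent, goal setting and randomisation all fall at Visit 1 ({26a}, {11a}, {16b}). Randomisation follows eligibility and consent; its order relative to the interview is not stated.

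**The case against.** The strongest reply is that nothing here is wrong. Regression on allocation and the minimisation variables is a valid intention-to-treat analysis, unbiased over repeated randomisation, and the trial was sized for a comparison without baseline. That stands. A reader might infer that the trial is underpowered or its estimate biased; Step 1 rules out the former by the plan's own calculation, and randomisation rules out the latter.

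Second, a reader might set the 0.48-point imbalance directly against the 0.8-point target. That overstates the matter. Only about r times the difference reaches the estimate, and the unadjusted confidence interval already allows for such variation. It is not an extra error on top of the interval.

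Third, r is unknown. Individually chosen goals rated two years later may correlate weakly with their starting ratings; at r = 0.2 the gain is about one percentage point of power. This stands, and it limits what can be claimed about size.

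Fourth, two further inferences fail. The 3.5 (SD 1.6) in {14} belongs to the external trial and is no evidence that this trial records a baseline score; Table 2 is. Nor does {20a} carry the identical model to the secondary and caregiver outcomes. It says the approach will be adapted, so their covariates are open and may properly be settled in the analysis plan.

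Fifth, the remedy needs a clean baseline. Patients are not blinded ({17a}), so a rating made after allocation could be influenced by it. This objection stands, and the fix has to deal with it.

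**Conclusion.** The point holds as a missed improvement to a stated model. {20a} names the covariates, Table 2 schedules the baseline score, and nothing else in the article brings that score into the primary estimate. The analysis as written remains valid at its planned 90% power.

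The gain from adjustment runs from about 1 percentage point of power (r = 0.2) to about 6 (r = 0.5), with the standard error falling from 0.245 to between 0.240 and 0.213 points. These figures assume 85 analysed per arm, SD 1.6 at both times, two-sided 5% and an r that the document does not supply. The extra precision would matter more if the true effect were smaller than planned: at 0.4 SD, power is about 74% unadjusted and 85% at r = 0.5. That the covariate helps little if r is low is no reason to omit it, because its cost is so small.

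**What to change.** In {20a}, add the baseline mean goal-attainment rating to the prespecified covariates of the primary model, alongside age and Hoehn and Yahr stage. State, there or in {18a}, that goals are set and this rating is taken in both arms before randomisation at Visit 1. When the approach is adapted to continuous secondary outcomes and to the Carer Experience Scale, include the baseline value of the measure where one is collected.

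The cost is one degree of freedom in the primary model and a stated order of procedures at Visit 1. No new data are needed if Table 2 is followed. Make the change before any outcome data are seen, so that it cannot look data-driven. If some ratings have already been taken after allocation, settle and document how those are handled before the score is used as a covariate.
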